### 2.9. Cost-Effectiveness Analysis

A cost-utility analysis will be conducted with a health system perspective in line with the methodological recommendations of health economists [70], and the guidelines defined in the scientific literature [18].

The study will be carried out considering the costs and health effects of the intervention, including the effect of Tele-SSE on the number of falls. Only the direct costs of the program (i.e. medication, primary care visits, and hospital admissions) will be considered. Likewise, the salaries of the person hired to carry out the video-conferences will be considered in agreement with the set-out guidelines, based on the corresponding collective agreement. It will also include the costs of the essential material for the Tele-SSE implementation, such as training mats, mobile phones, and Internet connection.

First, the average costs and effectiveness will be calculated for each group, i.e., the Quality Adjusted Life Years (QALYs) earned. Subsequently, the incremental cost-effectiveness ratio will be calculated [71] and various sensitivity analyses will be conducted, including probabilistic, which will be carried out with 1000 repetitions [72]. These replicas will be included in the cost-effectiveness plan and will be used to make the acceptability curve. Then, we will be able to see in which quadrant of the cost-effectiveness plan the Tele-SSE intervention is located, which will indicate whether the Tele-SSE has been costly and effective than the intervention made by the control group (usual care).

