### 2.3. Sample Size

The number of participants was calculated based on the change in quality of life assessed using the 5-level Euroqol-5D questionnaire (EQ-5D-5L). As far as we know, there are no available data on the minimum real change in the EQ-5D-5L in fibromyalgia patients, so we have used a reference of pathology that deals with pain, being this real minimum difference of 0.15 [19]. Therefore, a total of 118 participants (Experimental group; *n* = 59 and Control group; *n* = 59) are needed; accepting alpha and beta risks of 0.05 and 0.2, respectively, in a bilateral contrast, to detect a difference equal to or greater than 0.15 units. It is assumed that the common standard deviation of EQ-5D-5L is 0.26, taking as a reference one of the articles by the principal investigator of this project, which evaluated the health-related quality of life through this questionnaire [20]. A follow-up loss rate of 20% has been estimated. 

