### 2.4. Randomization and Blinding

After baseline assessments, all participants will be randomly assigned to two groups: Experimental (Tele-SSE) or control (usual care). A simple computer-generated randomization sequence will be created before participants are enrolled (1:1) using the computer software Research Randomizer (Version 4.0, Geoffrey C. Urbaniak and Scott Plous, Middletown, CT, USA) (http://www.randomizer.org). The randomization sequence will be made by a member of the research team without clinical participation in the trial. The assignment will be hidden in a password-protected computer file. Although participants will know their group assignment, outcome evaluators and data analysts will be blinded to the assignment.

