#### 2.7.1. Randomized Trial Main Measures

**Applicability.** The percentage of participants with FM who can perform the proposed training. If any participant is unable to perform the intervention, the cause will be noted.

**Safety.** A record shall be kept about any incidence, injury or problem during the sessions, as well as if possible, the origin of the problem.

**Number of falls in the last year and six months.** Participants will be asked about the number of falls that they have suffered in the past year and six months. The World Health Organization (WHO) definition of falls will be adopted, namely: “Involuntary events that cause the body to lose its balance and find itself on land or on another firm surface that stops it”.

**Incremental cost-effectiveness ratio.** The average cost of the intervention and the effects on health will be calculated for both intervention and control groups. The measurement of health effects is defined as Quality Adjusted Life Years (QALYs), which is calculated by multiplying the life years (life expectancy) with the quality of life of the participants [25]. The health-related quality of life will be evaluated using the EQ-5D-5L questionnaire [26] and this measure will be used for sample calculation. Incremental cost-effectiveness ratio will be calculated by dividing the difference between the average costs of both groups by the difference in mean QALYs gained in both groups. The utilities needed to calculate the QALYs will be computed for each set of health status using the algorithm available on the official website of the EuroQol group (http://www.euroqol.org/). The algorithm used to calculate the EQ-5D-5L utility index will be the “crosswalking” of the EuroQol levels Spanish version. This utility index is comprised between −0.654 (corresponding to the worst state of health and equivalent to 55555) and 1 (perfect state of health and equivalent to 11111).

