### 2.8. Statistical Analysis

Baseline characteristics of participants will be presented as the mean (standard deviation) for continuous variables and proportions for categorical variables. The normality will be checked using the Kolmogorov-Smirnov test. Then, two types of analyses will be performed: 1) An intention-to-treat analysis including all participants and 2) a per-protocol analysis using only those participants who complete the study.

**Intention-to-treat analysis.** This analysis will include all randomly assigned participants in their corresponding groups. Multiple imputations will be used to impute lost data. The effects of the intervention on the main and secondary variables will be computed using a repeated measures ANCOVA test, adjusted by age and baseline values. Results shall include the Cohen’s *d* effect size (95% confidence interval) and statistical significance for each dependent variable respect to time and its interaction effects (group × time). Statistical significance shall be established at the conventional level of *p* < 0.05. In sensitivity analyses, the data imputation will be made from the baseline patient data and from those participants who completed the study, in order to avoid estimation biases. 

**Analysis by protocol.** Similar analyses than those described above will be carried out, but only using participants who have attended at least 75% of the sessions.

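### The ICER is built from a difference in group mean QALYs with no baseline-utility term, and the baseline-adjusted model in section 2.8 is not linked to it, so avoidable chance error enters a primary outcome

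*Protocol article*

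**What the plan says.** - Protocol article, section 2.7.1, defines a QALY as time multiplied by the quality-of-life level, with EQ-5D-5L supplying the utility. It obtains the ICER by "dividing the difference between the average costs of both groups by the difference in mean QALYs gained in both groups".
- Section 2.9 gives the order of work: "First, the average costs and effectiveness will be calculated for each group, i.e., the Quality Adjusted Life Years (QALYs) earned". The ratio follows, then sensitivity analyses, including a probabilistic one with 1000 repetitions that feeds the cost-effectiveness plane and the acceptability curve.
- Section 2.8 says that effects on main and secondary variables will be "computed using a repeated measures ANCOVA test, adjusted by age and baseline values". The outputs named there are Cohen's d with its confidence interval and statistical significance for time and for group by time.
- Section 2.4: "A simple computer-generated randomization sequence will be created". No stratification is described.
- The Abstract lists the ICER as the fourth primary outcome. Table 2 schedules it at baseline, month 12 and month 13.

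**The concern.** Utility at follow-up is usually correlated with utility at baseline. In some QALY forms, baseline utility is also part of the QALY itself. If one arm happens to start with higher utility, an unadjusted difference in mean QALYs absorbs part of that head start. If QALYs are taken as change from baseline, it absorbs part of the reverse through regression to the mean.

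Section 2.8 shows that the authors see the value of baseline adjustment, but that model does not reach the ratio as written. The ICER has no value per participant, so an ANCOVA cannot be run on it directly, and section 2.9 does not say that adjusted means enter the denominator.

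At stake is the precision of the QALY difference, and with it the ICER, the plane and the acceptability curve. Repetitions that resample the observed data, or simulate around the observed means, would carry a realised imbalance forward and would not remove it. The Discussion intends to take the cost-effectiveness result to health policy decision-makers and insurers.

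**Working it through.** **Inputs from section 2.3.** Error rates: "accepting alpha and beta risks of 0.05 and 0.2, respectively, in a bilateral contrast". Target: "to detect a difference equal to or greater than 0.15 units". Spread: "the common standard deviation of EQ-5D-5L is 0.26". Attrition: "A follow-up loss rate of 20% has been estimated". Planned size: 59 per arm.

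**Assumed, because the article does not give them.** The correlation r between baseline and month-12 utility is 0.4 to 0.7, with equal SD at both times. The QALY form is also not fixed, so three are shown. The age term and the small cost of estimating the regression slope are ignored.

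**The plan's own figure.** n per arm = 2 × [(1.960 + 0.842) × 0.26 / 0.15]² = 47.16. With 20% loss, 47.16 / 0.8 = 58.95, so 59 per arm and 118 in all. The figure reproduces and is not in dispute.

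**Chance baseline difference.** SE = 0.26 × √(2/59) = 0.0479. The 95% range is ±1.96 × 0.0479 = ±0.094. The chance of an absolute imbalance above 0.05 is about 30%. With 47 per arm (59 × 0.8), the SE is 0.0536 and that chance is about 35%.

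**Effect of a one-SE imbalance on the unadjusted QALY difference.** Let u0 and u12 be baseline and month-12 utility.

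- Month-12 form, u12 × 1 year: shift = r × 0.0479; expected gain 0.15.
- Two-point area under the curve, (u0 + u12)/2: shift = (1 + r)/2 × 0.0479; expected gain 0.15/2 = 0.075, if the effect builds linearly to month 12.
- Change from baseline, (u12 − u0)/2: shift = −(1 − r)/2 × 0.0479; expected gain 0.075.

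The unadjusted SE is 0.0479 times 1, √((1 + r)/2) and √((1 − r)/2) respectively. The adjusted SE is 0.0479 × √(1 − r²) for the first form and half of that for the other two.

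| QALY form | Shift, r = 0.4 | Shift, r = 0.7 | Share of expected gain | Unadjusted SE, r = 0.4 / 0.7 | Adjusted SE, r = 0.4 / 0.7 |
|---|---|---|---|---|---|
| Month 12 × 1 year | 0.019 | 0.034 | 13% to 22% | 0.048 / 0.048 | 0.044 / 0.034 |
| Two-point area under the curve | 0.034 | 0.041 | 45% to 54% | 0.040 / 0.044 | 0.022 / 0.017 |
| Change from baseline | −0.014 | −0.007 | −19% to −10% | 0.026 / 0.019 | 0.022 / 0.017 |

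**What this does to the ratio, in the area-under-the-curve case only.** At r = 0.6 the shift is 0.8 × 0.0479 = 0.0383, or 51% of 0.075. With the cost difference held constant, the ICER is multiplied by 1/1.51 = 0.66 or 1/0.49 = 2.0, depending on which arm starts higher. The SE falls from 0.043 to 0.019 with adjustment. Over r = 0.4 to 0.7, the chance of an estimated gain of zero or below despite the planned effect is about 3% to 4.5% unadjusted and about 0.03% or less adjusted.

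**A by-product of adjustment.** The area-under-the-curve and change forms differ by exactly u0: (u0 + u12)/2 − (u12 − u0)/2 = u0. Once u0 is a covariate, both give the same arm coefficient, so the choice between those two forms no longer affects the QALY difference.

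**The case against.** **The text never says the means are unadjusted.** Section 2.7.1 gives the generic definition of an ICER, which would equally describe a ratio of adjusted means. Section 2.8 promises baseline adjustment for the main variables, and the ICER is listed among them. A reader might infer that the plan commits to raw means. The documents do not support that: they are silent on the link. What stands is that the only formula given for this primary outcome has no baseline term, and that sections 2.8 and 2.9 are not joined.

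**The mechanism depends on a QALY form that is not fixed.** A reader might infer that each arm's baseline utility is credited as QALYs gained, or that the 45-54% shift is the size of the problem. Both hold only in the area-under-the-curve case. In the month-12 form, baseline acts only through correlation. In the change form, the sign reverses. A utility level common to both arms cancels in the difference, so only imbalance matters. This objection stands in full on size and direction. It does not remove the point, because adjustment improves precision in all three forms.

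**There is no systematic bias.** Under randomisation the unadjusted difference in mean QALYs is correct on average. A reader might call the ICER biased; it is a matter of chance error. This too stands.

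**This is analysis-plan detail.** The article condenses a protocol, no analysis plan is shown, and section 2.9 refers to guidance that is not reproduced. Regression details would indeed belong elsewhere. The formula for a primary outcome is stated here, however, and can be improved where it is stated.

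**Conclusion.** The concern holds as a matter of precision and of reconciling sections 2.7.1, 2.8 and 2.9. Followed as written, the ICER denominator is a difference in group mean QALYs without baseline adjustment. It is unbiased in expectation but noisier than it needs to be.

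For correlations of 0.4 to 0.7, a one-SE chance imbalance moves the denominator by between roughly 10% and 54% of the expected gain, with a sign that depends on the QALY form. The gain from adjustment is largest for the two-point area under the curve and modest for the other two forms. The SD, target difference and sample size are the plan's own. The correlation, the QALY forms and the linear build-up of effect are assumptions. The plan should make this change because it costs little and affects a primary outcome. It is not an error that invalidates the design.

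**What to change.** In sections 2.7.1 and 2.9, state that the QALY difference in the ICER is the arm coefficient from a regression of participant-level QALYs on arm, baseline EQ-5D-5L utility and age. Age and baseline value are already the covariates of section 2.8. State also that the 1000 repetitions use this adjusted estimate: refitted in each resample if they are a bootstrap, or drawn from its estimated distribution if they are parametric. Section 2.9 does not say which, so the sentence should. Keep the unadjusted group means as descriptive results.

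No new data are needed, since baseline utility and age are already collected. The cost is a short addition to the text and somewhat more analysis work, chiefly in combining the regression and the repetitions with the multiple imputation planned in section 2.8. Fixing this before analysis also prevents a choice between adjusted and unadjusted ICERs once the results are known.

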## 3. Discussion

This project would be the first that uses the Tele-SSE training system for falls prevention in fibromyalgia people and, to our knowledge, the first study carried out in Spain using the SSE training system. If the effectiveness of this treatment for falls prevention and its cost-effectiveness compared to conventional treatment (usual care) is demonstrated, this would pose an economic saving opportunity to the health system. It would also help to implement this type of methodology in the health system, not only for fibromyalgia patients, but also for people with an increased risk of falls, such as frail elderly; a population where the efficacy of SSE training has recently been shown [13]. It would also have great repercussions, since ageing of the population, according to all statistical projections, will increase in the next years [73,74].

In addition, to our knowledge, this would be the first study that would show the cost-effectiveness of Tele-SSE. Thus, if the effectiveness and cost-effectiveness of this training system are proven, it could be applied by several agents, which could be interested in taking advantage of the benefits of these types of activities. It should be assumed that this training method does not require any specific installation and may be carried out indoors or outdoors. Therefore, due to this being a low-cost healthcare technology that can be easily standardized by levels of difficulty (see methodology), its implementation in both public and private sectors would not pose any problems.

Moreover, the main measure of the additional focus group study proposed will revolve around investigating the acceptability of Tele-SSE in the agents of the social-sanitary system. Thus, key factors will also be identified for its transfer to the public and private social-sanitary system. Regarding the public sector, after a focus group with the main health policy decision-makers, where the applicability and acceptability of this health technology would be analyzed, these decision-makers would be urged to include the Tele-SSE within the recommendations offered by health professionals to fibromyalgia people for better management of the disease. Furthermore, we would encourage the application of Tele-SSE or SSE within the services offered by public health programs, such as the so-called “Exercise Looks After you” [75], increasing its cost-effectiveness in everything related to falls prevention in fibromyalgia patients, and even being extrapolated to other populations with increased risk of falls, such as frail elderly. Likewise, the possibility of implementing this training system in different associations of diseases associated with high risk of falls (e.g., fibromyalgia, multiple sclerosis, Parkinson’s disease) and at home (e.g., for elderly) would be studied. In the private sector, the focus group study would include the heads of health and sports centers, focusing on the applicability of Tele-SSE in their centers and showing the results of the study in order to highlight the potential advantages of applying Tele-SSE or SSE in the private sector. Also, meetings would also be held with heads of insurance companies to see the possibility of including discounts or life insurance with special conditions for those people who regularly carry out Tele-SSE training.

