Fibromyalgia (FM) is a chronic syndrome that affects 3.43% of women worldwide, 3.90% in Europe, and 4.2% in Spain [14]. This syndrome has a considerable functional impact on people who suffer from it, as they present chronic pain problems requiring many social, health, and work resources through comprehensive and continuous care [15]. It is estimated that people with FM represent an annual expense of 11,629.03 euros per patient and year in Spain, costing a total of 4223.02 million euros to Spanish health services, which poses a 279.10-euro cost per inhabitant and year [14]. If we consider that, according to the Ministry of Health of Extremadura, a health expenditure of 1549 euros per inhabitant was made in 2016, the expense on fibromyalgia represents 18% of the total health cost per inhabitant in Extremadura. Therefore, any intervention that may help to reduce these percentages could have a positive impact on reducing the costs of the Extremadura health system.

Falls in people with FM amount to 2.5 per year compared to 0.5 for people without FM [16]. Thus, part of the annual health costs of this syndrome comes from falls. The project that we are presenting attempts to reduce costs associated with falls in this population through balance training with the SSE method, conducted by a professional through video-conferencing (Tele-Square Stepping Exercise; Tele-SSE), improving the balance and preventing falls in women with FM. Reviewing the scientific literature, the SSE program appears to improve balance by preventing falls and decreasing the fear of falling in older adults [13], but no publication had studied the benefits of SSE in people with FM.

Therefore, the main objectives of this project are 1) to investigate the applicability, safety, decrease in the number of falls, and incremental cost-effectiveness ratio of a prevention of falls program through Tele-SSE in women with FM, and 2) to identify key factors for its transfer to the public and private social health system, evaluating the acceptability of Tele-SSE in the agents of the social health system in charge of including Tele-SSE in their services offer.

Additionally, this project has a secondary aim to evaluate the effect of Tele-SSE on balance levels, fear of falling, body composition, physical fitness, quality of life related to health and positive health, pain, disability level, depressive symptoms, and cognitive aspects of participants.

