#### 2.7.2. Focus Group Main Measure

Once the randomized controlled trial has been carried out, and considering its preliminary results, a focus group will be set up around questions previously drawn up by the research group, in order to determine the acceptability of Tele-SSE in the social-sanitary system agents. Key factors will also be identified for its transfer to the public and private social-sanitary system. The transcripts will be analyzed with the support of specific software for discourse analysis, which will be used to organize and classify the data into categories and then proceed to order and analyze them [27].

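### The private-sector focus group is described as promoting Tele-SSE in the same session that measures its acceptability, which risks tilting those answers towards acceptance

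*Protocol article*

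**What the plan says.** Section 1 (Background) of the protocol article names two main objectives. The second is to identify what matters for transfer to the public and private system, "evaluating the acceptability of Tele-SSE in the agents of the social health system in charge of including Tele-SSE in their services offer".

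Section 2.7.2 (Focus Group Main Measure) describes the instrument: "Once the randomized controlled trial has been carried out, and considering its preliminary results, a focus group will be set up". It is built around "questions previously drawn up by the research group, in order to determine the acceptability of Tele-SSE in the social-sanitary system agents". On analysis it says: "The transcripts will be analyzed with the support of specific software for discourse analysis". The purpose as worded there is neutral.

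Section 3 (Discussion) describes two strands:

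- **Private sector.** The participants are the heads of health and sports centres, and the content includes "showing the results of the study in order to highlight the potential advantages of applying Tele-SSE or SSE in the private sector".
- **Public sector.** Acceptability is analysed in a focus group with health policy decision-makers. After it, "these decision-makers would be urged to include the Tele-SSE within the recommendations offered by health professionals".

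**The concern.** A focus group meant to find out whether potential providers accept a service should not also be the occasion for persuading them. If the team that ran the trial presents its results with the declared aim of bringing out the advantages, participants may voice more acceptance, and fewer barriers, than they would after a neutral summary. What the transcripts record is then a mix of the agents' own judgement and the effect of the presentation. Sorting the transcripts into categories afterwards cannot separate the two.

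The focus group is the only data source the article describes for acceptability to these agents. A bias in one strand would therefore weaken what can be said about private-sector transfer under main objective 2.

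**Working it through.** No arithmetic applies: the protocol gives no number of focus groups, no number of attendees, and no threshold for acceptability. The check is a side-by-side reading.

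1. **Is acceptability a main measure?** Yes. Section 1 places it within the second main objective, the heading of section 2.7.2 calls it the main measure of the focus group, and section 3 repeats this.

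2. **Is the stated purpose the same in both sections?** No. Section 2.7.2 sets out to determine acceptability, which leaves the answer open. For the private-sector group, section 3 adds a second purpose, to highlight advantages, which fixes the direction of the presentation.

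3. **Does the promotional wording belong to the focus group or to later dissemination?** To the focus group. The clause stands in the same sentence that says who will take part in the private-sector focus group. Meetings with insurers follow in a sentence of their own, as a separate activity.

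4. **Does it reach the public-sector strand?** Not as written. No sentence says that the decision-makers are shown results in order to highlight advantages. The urging comes after the focus group in which their views are analysed, so it cannot change answers already recorded. It shows the team's stance and is not a mechanism of bias.

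5. **Is promotion tied to the trial's findings?** Not in the sentences that describe the two strands. Earlier in section 3, however, application is tied to demonstrated effectiveness and cost-effectiveness, and section 4 (Conclusions) ties it to effectiveness and safety. The condition is implied nearby but not written where it is needed.

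6. **Which results are used?** Section 2.7.2 has the group formed "considering its preliminary results". Table 2 schedules falls and the cost-effectiveness ratio at both month 12 and month 13, and section 2.9 plans a probabilistic sensitivity analysis with 1000 repetitions to show the uncertainty of the ratio. The text does not say that preliminary results would lack these data, nor that they would include them.

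The direction of the risk follows from step 2: towards acceptance, in the private-sector strand.

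**The case against.** The strongest reply is that the Methods govern conduct and are neutral, while the promotional clause is conditional Discussion prose about transfer, itself an aim of the project. The topic guide, the order of questions and the material shown are details that a condensed article leaves to the full protocol. Agents also need to see results to judge a service, so showing them is no flaw. The focus group is an additional qualitative study with no test or decision rule attached.

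Much of this stands. The missing guide is not a finding, and neither is showing results. But the clause at issue is a stated purpose, not a missing detail, and it differs from the purpose in section 2.7.2. Someone who followed section 3 as written would present the results with a one-sided aim in the session that measures acceptability.

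A reader might go further and infer three things that the article does not support:

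- **That the whole of objective 2 is steered towards acceptance.** The promotional wording covers only the private-sector group, and the urging of public decision-makers follows their focus group.
- **That agents will be shown only the advantages.** The text says that the results of the study will be shown. It does not say that harms, null findings or costs will be withheld.
- **That adoption will be pressed whatever the trial finds.** Sections 3 and 4 make application depend on proven benefit, even though the sentence on urging does not repeat this.

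**Conclusion.** The point holds in a narrow form. In the private-sector focus group, section 3 combines promotion with measurement, at odds with the neutral purpose in section 2.7.2. This creates an avoidable risk of bias towards acceptance in one strand of one main objective. That the bias would in fact occur is an inference: it assumes that the session is run as section 3 describes and that the framing of the results influences what participants say. Its size cannot be estimated from the document.

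The public-sector strand, the falls outcome, the cost-effectiveness ratio and the randomized comparison are untouched by this wording. Severity is low.

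**What to change.** Reconcile sections 2.7.2 and 3 as follows:

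1. Give all focus groups, public and private, the same balanced summary of the trial: falls, safety, adherence, costs and the incremental cost-effectiveness ratio, with their uncertainty and whatever their direction.
2. Collect views on acceptability and barriers before any promotion.
3. Move promotion or urging to a separate, later occasion, and make it explicitly conditional on the results, as sections 3 and 4 already imply.
4. Reword the private-sector sentence in section 3 so that the aim of showing the results is to inform the discussion.
5. Preferably use the final month-12/13 results and not preliminary ones.

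The cost is rewording and a change in the order of events. The one downside is a short wait if the groups are held after the final analysis.
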